## Abstract

**Background:**

As the number of cardiac diseases continuously increases within the last years in modern society, so does cardiac treatment, especially cardiac catheterization. The procedure of a cardiac catheterization is challenging for both patients and practitioners. Several potential stressors of psychological or physical nature can occur during the procedure. The objective of the study is to develop and implement a stress management intervention for both practitioners and patients that aims to reduce the psychological and physical strain of a cardiac catheterization.

**Methods:**

The clinical study (DRKS00026624) includes two randomized controlled intervention trials with parallel groups, for patients with elective cardiac catheterization and practitioners at the catheterization lab, in two clinic sites of the Ernst-von-Bergmann clinic network in Brandenburg, Germany. Both groups received different interventions for stress management. The intervention for patients comprises a psychoeducational video with different stress management technics and additional a standardized medical information about the cardiac catheterization examination. The control condition includes the in hospitals practiced medical patient education before the examination (usual care). Primary and secondary outcomes are measured by physiological parameters and validated questionnaires, the day before (M1) and after (M2) the cardiac catheterization and at a postal follow-up 6 months later (M3). It is expected that people with standardized information and psychoeducation show reduced complications during cardiac catheterization procedures, better pre- and post-operative wellbeing, regeneration, mood and lower stress levels over time. The intervention for practitioners includes a Mindfulness-based stress reduction program (MBSR) over 8 weeks supervised by an experienced MBSR practitioner directly at the clinic site and an operative guideline. It is expected that practitioners with intervention show improved perceived and chronic stress, occupational health, physical and mental function, higher effort-reward balance, regeneration and quality of life. Primary and secondary outcomes are measured by physiological parameters (heart rate variability, saliva cortisol) and validated questionnaires and will be assessed before (M1) and after (M2) the MBSR intervention and at a postal follow-up 6 months later (M3). Physiological biomarkers in practitioners will be assessed before (M1) and after intervention (M2) on two work days and a two days off. Intervention effects in both groups (practitioners and patients) will be evaluated separately using multivariate variance analysis.

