### Sample Size Determination

We calculated the sample size for two patient groups for two measurement points based on a pilot study. The sample was powered to assume a medium effect size (*d* = 0.25) and a minimum detectable clinical difference of 0.5 standard deviation on the (z-standardized) main criterion: perceived stress. For the main criterion, the power for significant group differences is 1-β = 0.93 with a case number of *N* = 60 people per group (38). As the sample for the practitioners was limited to all members of the catheterization lab of the clinic who fulfill the inclusion criteria, a sample size determination was not required.

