### Outcomes

The primary outcomes for patients are reduced complications and less sedative medication during CC (documented by nurses at the CC lab), and less tension/strain (physiological parameters like pulse, blood pressure, heart frequency), perceived stress (PSS) and better mood (POMS) measured by established and validated self-report questionnaires. Further secondary outcomes for patients are better pre- and post-operative wellbeing, chronic stress (TICS), depression and anxiety (HADS), panic disorder, psychosocial functioning (PHQ-9), life events (ILE), general health (SF-12), satisfaction with health and sleep (41). Additionally, patients are asked about their life style, socioeconomic status and satisfaction about the intervention. At the CC lab, nurses document the behavior of the patients during the cardiac catheterization (agitation, duration of hospital stay, tranquilizer/sedativa use, and level of information) and the number of complications occurred during the procedure. The primary outcomes for practitioners—perceived (PSS) and chronic stress (TICS)—are measured by established and validated self-report questionnaires. Additionally, stress load and recovery are assessed by physiological measurements: circadian profile of HRV (42–44), saliva cortisol (45), alpha-amylase (46) and lysozyme on two working/lab days and two days off as well as the following night, prior to and after the intervention, respectively. The HRV measurements base on beat-to-beat R-R intervals and comprises outcomes for the total activity of the autonomic nervous system [standard deviation of RR intervals (SDNN)], parasympathetic function [root mean sum of squared distance (RMSSD)] and stress load and recovery (number and percentage of R-R intervals lower or >50 msec). Saliva samples are taken on nine defined time points during the day (immediately after awakening, 30, 45, 90, 150 min after awakening, before lunch, 4 p.m., before dinner and going to bed) on a working/lab day and day off. Weight and mood (POMS) are assessed simultaneously as control variables. The practitioners are further asked about vital exhaustion (VE), anxiety and depression (HADS), tension, effort-reward imbalances (ERI), social support (BSSS), satisfaction with health and sleep (41) as well as life style, socioeconomic status, expectations and adherence (barriers) to the intervention program.

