Details on outcomes, questionnaires and measurement points are provided in Table 1 for participants and Table 2 for practitioners.

**Table 1 T1:** Outcome measurements for patients with elective cardiac catheterization.

**Outcome**	**Measurement**	**Assessment**		
		**M1** **(day before CC)**	**M2** **(day after CC)**	**M3** **(6 months after M1)**
Chronic stress	Trier inventory for chronic stress (TICS) (47)	X		X
Perceived stress	Perceived stress scale-−10 items (PSS-10) (48, 49)	X		X
Life events	Inventory of stressful life-events (ILE) (50)		X	
Depression	Patient health questionnaire-−9 items (PHQ-9) (51)	X		X
Anxiety and depression	Hospital anxiety and depression scale (HADS) (52, 53)	X	X	
Health-related quality of life	Short form health-−12 items (SF-12) (54)	X		X
Pain	Visual analog scale (VAS)	X	X	X
Mood	Profile of mood state (POMS) (55, 56)	X	X	
Satisfaction with health and sleep	Visual analog scale (VAS)	X	X	X
Life style factors	Physical activity, smoking, alcohol consumption, medication, critical life events	X		X
Sociodemographic characteristics	Sex, Age, education, marital status, job position, income	X		
Satisfaction with intervention			X	
Behavior while CC*				
Physiological parameter while CC*	Pulse, blood pressure, heart frequency	X	X	

**(additional) measurement during CC*.

**Table 2 T2:** Outcome measurements for practitioners at the catheterization lab.

**Outcome**	**Measurement**	**Assessment**		
		**M1** **(before intervention)**	**M2** **(after intervention)**	**M3** **(6 months after M1)**
Chronic stress	Trier inventory for chronic stress (TICS) (47)	X		X
Perceived stress	Perceived stress scale-−10 items (PSS-10) (48, 49)	X		X
Effort-reward imbalances	Effort-reward imbalances questionnaire (ERI) (57)	X		X
Anxiety and depression	Hospital anxiety and depression scale (HADS) (52, 53)	X	X	
Vital exhaustion	Maastricht vital exhaustion questionnaire (VE) (58)	X	X	
Tension	Visual analog scale (VAS)	X	X	X
Mood	Profile of mood state (POMS) (55, 56)	X	X	
Satisfaction with health and sleep	Visual analog scale (41)	X	X	X
Life style factors	Physical activity, smoking, alcohol consumption, medication, critical life events	X		X
Social support	Berlin social support scale (BSSS) (59)		X	
Sociodemographic characteristics	Sex, age, education, marital status, job position, income	X		
Expectation of/satisfaction with intervention		X	X	
Heart rate variability	Activity of the autonomic nervous system (SDNN), parasympathetic function (RMSSD)	X	X	

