
Both stress-management intervention for patients and practitioners are expected to have beneficial effects on the involved individuals. We expect to significantly minimize tension, perceived stress during the cardiac catheterization in patients of the intervention group. Additionally, we expect a favorable effect on physiological outcome like heart rate, blood pressure (in patients) and heart rate variability (in practitioners). An effective stress reduction should be favorable for the individual patients but it should further prevent complications and stressful incidents during the cardiac catheterization. On this account a successful patient intervention may add to less hazard and more safety in the workplace, improved working conditions and occupational safety, preservation of earning capacity, avoidance of participation restrictions and loss of performance for the practitioners. These positive aspects of work safety for the staff members of the catheterization lab should additionally pay off for patient security and satisfaction. The study may add knowledge how to eliminate stressful exposures and to contribute to more (psychological) security, less output losses and exhaustion during work.

All evaluated guidelines, materials for the psychoeducational intervention in patients and MBSR intervention in practitioners should be transferred in clinical routines.

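### The primary stress questionnaires (PSS-10 in both trials, TICS in practitioners) are scheduled at M1 and M3 only, which conflicts with the abstract and, for patients, with the effect expected during catheterization

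*Protocol article*

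**What the plan says.** **Which outcomes are primary.** In the Protocol article, Outcomes, the patient primaries are complications and sedative use during the catheterization, physiological strain, and "perceived stress (PSS) and better mood (POMS) measured by established and validated self-report questionnaires". For practitioners the same section states: "The primary outcomes for practitioners—perceived (PSS) and chronic stress (TICS)—are measured by established and validated self-report questionnaires". The practitioners' HRV and saliva measures are introduced as additional to these.

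**What the patient trial is powered on.** Sample Size Determination covers two patient groups at two unnamed measurement points. It identifies the target as the ("z-standardized) main criterion: perceived stress". There is no calculation for practitioners.

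**When outcomes are measured, according to the abstract.** The Methods paragraph says that primary and secondary practitioner outcomes "will be assessed before (M1) and after (M2) the MBSR intervention and at a postal follow-up 6 months later (M3". The patient sentence likewise lists the day before, the day after and 6 months.

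**When they are measured, according to the tables.** The rows for "Trier inventory for chronic stress (TICS) (47" and for the perceived stress scale, "items (PSS-10) (48, 49", carry a mark at M1 and M3 and a blank at M2. This holds in both Table 1 and Table 2.

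**What effect is expected.** In the Discussion: "We expect to significantly minimize tension, perceived stress during the cardiac catheterization in patients of the intervention group".

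**The concern.** The scales named as primary are missing from the visit closest to the intervention, while other scales are collected at that visit.

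For practitioners this affects every outcome that the Outcomes section calls primary. The trial could not show whether stress scores had moved by the end of MBSR. A benefit that faded before 6 months would look the same as no benefit. The stress questionnaires (M1, M3) and the HRV and cortisol data (M1, M2) would also share no time point after baseline, so the two could not be set side by side.

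For patients, the criterion that sets the sample size would be read 6 months after a 10-minute video about one procedure. The Discussion's expectation about perceived stress during that procedure has no PSS reading behind it. Values not collected at M2 cannot be recovered later.

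**Working it through.** This is a comparison of schedules. Status comes from Outcomes, and marks come from Tables 1 and 2.

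| Outcome | Trial and status | M1 | M2 | M3 |
|---|---|---|---|---|
| PSS-10 | patients, primary and powered | X | blank | X |
| PSS-10 | practitioners, primary | X | blank | X |
| TICS | practitioners, primary | X | blank | X |
| POMS | patients, primary | X | X | blank |
| Pulse, blood pressure, heart frequency | patients, primary | X | X (also during the procedure) | blank |
| Complications, sedatives | patients, primary | – | recorded during the procedure | – |
| HADS, vital exhaustion | practitioners, not primary | X | X | blank |
| Tension VAS | practitioners, not primary | X | X | X |
| HRV, saliva cortisol | practitioners, additional | X | X | blank |

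1. **Count.** Of the three primary stress-questionnaire entries, 0 of 3 are marked at M2 and 3 of 3 at M1 and M3. Patient TICS has the same pattern but is secondary.

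2. **Is the blank real?** The PSS-10 and TICS rows are identical in both tables, and neighbouring rows do carry M2 marks. A fault in reading the table is unlikely.

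3. **Does the visit label in Study Design rescue it?** That section labels the practitioner visit after the 8-week programme M3, and also labels the 6-month visit M3. The Table 2 header defines M2 as after the intervention and M3 as 6 months after M1. The label therefore looks like a slip, and the PSS and TICS marks belong to the 6-month visit.

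4. **Delay, practitioners.** Assume MBSR starts at M1. Six months is about 26 weeks, and 26 − 8 = 18 weeks, or about 4 months between the end of MBSR and the first PSS or TICS reading. A later start shortens this gap.

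5. **Delay, patients.** The video is shown on the admission day, which is M1, so the first PSS reading afterwards comes about 6 months later.

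6. **Which two points does the power calculation use?** Table 1 gives PSS-10 only at M1 and M3. If perceived stress means PSS-10, as Outcomes and Table 1 indicate, the powered comparison can only be M1 to M3.

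7. **Side check on the stated power of 0.93** (60 per group, two-sided 0.05). The point does not depend on it. With power = Φ(δ√(n/2)/σ − 1.96), 0.5 SD at a single time point gives Φ(0.5 × √30 − 1.96) = Φ(0.78) = 0.78. Adjusting for baseline with an assumed correlation of 0.6 replaces σ by √(1 − 0.6²) = 0.8 and gives Φ(2.739/0.8 − 1.96) = Φ(1.46) = 0.93. A repeated-measures group comparison with f = 0.25 gives 0.94 to 0.92 for correlations of 0.2 to 0.3. The figure therefore depends on a model and a correlation that the article does not state, and can be neither confirmed nor refuted. It does show that changing the measure or the time point would change the basis of the power statement.

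**The case against.** **The abstract may only be listing visits.** Its sentences cover primary and secondary outcomes together, and its next practitioner sentence limits biomarkers to M1 and M2. It cannot mean every instrument at every visit. It also expects lower patient stress over time, which an M1/M3 schedule can address, and two measurement points in the sample size section fit M1/M3. This stands as a reading of the abstract's style. It does not remove the conflict for practitioners: both outcomes named primary are absent at M2, so the sentence holds for the set of outcomes but for no primary.

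**A reader might infer that patient stress around the procedure goes unmeasured, or that a null PSS result at M3 would leave the patient question unanswered.** The article does not support that. POMS and the physiological parameters are patient primaries measured at M2. Complications and sedative use are primaries recorded during the procedure, and HADS is also taken at M2. The research questions extend to anxiety, complications, hospitalization, recovery and well-being.

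**A reader might also infer that post-MBSR stress goes unmeasured.** It does not: tension VAS, vital exhaustion, HADS, HRV and cortisol are all collected at M2. Practitioner data are to be analysed mainly descriptively, without a power calculation. The gap is confined to the two named primaries. Practitioner POMS should not be cited as a secondary scale collected in their place, because Outcomes treats it as a control variable.

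**The omission may be deliberate.** Repeating a general stress scale a day or so after baseline may have seemed pointless. The article does not say so, and the reason would not carry over to a visit 8 weeks after baseline.

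**Postal loss at M3** is a lesser point, since telephone contact and a prepaid envelope are planned.

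**Conclusion.** The point holds, limited to the stress questionnaires. PSS-10 in both trials and TICS in practitioners have no M2 assessment. This contradicts the abstract for both trials and the Discussion's expectation for patients.

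The practitioner half is the more serious. Both named primaries skip the end of the programme, and the first reading comes about 4 months later, assuming MBSR starts at M1. For patients, the consequence is that the powered criterion tests perceived stress at 6 months rather than around the procedure, assuming that perceived stress in the sample size section means PSS-10. The peri-procedural claim can still be examined through other primaries. The conclusion should not be widened to all primary outcomes.

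**What to change.** **Practitioners.** Add PSS-10 and TICS to the existing M2 questionnaire. Name M2 as the post-intervention time point and M3 as the test of durability. The cost is a few questionnaire minutes at a visit already planned, plus an amendment. Study Status reports that first participants are already recruited and assessed, so anyone past M2 will lack these values. Report how many, and do not fill the gap from M3.

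**Patients.** State that the PSS main criterion is compared at M3 (M1 to M3). Rest the Discussion's peri-procedural claim on primaries already measured at M2 or during the procedure, namely POMS and the physiological parameters. This changes text only.

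**Consistency.** Make the abstract, Study Design, Sample Size Determination, Discussion and both tables agree. This includes the doubled M3 label for practitioners in Study Design. It also includes patient M2, which is the examination day in Study Design but the day after in Table 1.

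**What to avoid.** Do not reword PSS-10 to refer to the hospital stay, because the plan relies on its being an established and validated scale. If the main criterion is instead moved to an M2 measure such as POMS, the power calculation must be restated for that measure, with its model and assumed correlation.

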**Discussion:**

This study evaluates the effectiveness of two stress management intervention programs for patients and practitioners within cardiac catheter laboratory. Study will disclose strains during a cardiac catheterization affecting both patients and practitioners. For practitioners it may contribute to improved working conditions and occupational safety, preservation of earning capacity, avoidance of participation restrictions and loss of performance. In both groups less anxiety, stress and complications before and during the procedures can be expected. The study may add knowledge how to eliminate stressful exposures and to contribute to more (psychological) security, less output losses and exhaustion during work. The evolved stress management guidelines, training manuals and the standardized patient education should be transferred into clinical routines.

## Introduction

Cardiovascular diseases and their treatment are steadily rising in modern society and cardiac catheterizations are considered as a low risk, routine diagnostic procedures in this realm (1). In 2014, ~885.000 cardiac catheterizations and 342.000 interventions were conducted in Germany. In 2019, 836.202 left heart cardiac examinations and 297.094 percutaneous catheter intervention (PCI) were examined, an increase of 3.3 and 0.5%, respectively, compared to the previous year (2). The rising numbers of examinations entailed an increased workload by a nearly constant number of practitioners. Consequently, the time of preparation and post processing for the cardiac catheterization examination decreases as well as the recovery time for the practitioners between the examinations. No control over workload and hectic work environment are two factors that were most strongly associated with distress and burnout in cardiologists (3, 4). Beside the tremendous impact of burnout for the individual physician, like greater risks for alcohol and substance abuse and suicide, it also negatively impacts patient care (4). Systematic reviews have shown that physicians' burnout are associated with suboptimal quality of care and patients safety (5). Stress overload and burnout in physicians may consequently result in medical errors and ultimately add to the ~19.000 dead patients very year due to treatment errors (6). Medical errors are often associated with feelings of guilt and shame that often adds further to distress and depressive states in physicians (7, 8). In addition, ‘fatigue due to long duty hours‘ and ‘having other things to take care of‘ were identified as two the most common self-reported reasons for medical errors (7).

Cardiac catheterizations are challenging for both practitioners and patients: there are physical and psychological stress factors that are afflicted with uncertainty and high demands during this procedure. But practitioners and patients are afflicted differently by different stressors. For practitioners several potential sources of stress had been identified during the cardiac catheterization examination. Physical stressors range from restricted respiration and dehydration to orthopedic strain, chronic work-related pain, increased body temperature and limited mobility caused by surgical masks and 5–8 kg heavy lead apron as a protection against radiation (6). Besides the physical stress, practitioners are also exposed to a high psychological demand. They have to be highly concentrated under time pressure and may be confronted with complications that can be life threatening for their patient. In other words, practitioners can be under physical and mental strain during a cardiac procedure that triggers the stress response and releases stress hormones. Sympathetic over parasympathetic activation is key feature of the stress response and can be measured by heart rate variability. In addition, increased stress leads to a reduced mental flexibility and capability which might have an impact on the result of the cardiac catheterization procedure (9). Thus, chronic stress does not only affect the health of cardiologists (10, 11), it also has an impact on the surgical performance and therefore on patients health and safety (12–14). Therefore, it seems almost inevitable to implement preventive interventions that are on the one hand successfully reduce perceived distress and tension in practitioners and on the other hand are efficient in time and costs and fit in to the daily routines of the clinic. Mindfulness-based intervention are evaluated to substantial lessen symptoms of stress, depression and anxiety and improve quality of life and physical capability (15).

On the other side of the surgical table, a cardiac catheterization is often an anxiety-provoking and inscrutable procedure for the patients as its concerns the examination of an essential organ, the heart (6, 16). Most patients appraise an impending cardiac catheterization as a threat of harm or challenge and experience psychological distress. Feelings of anxiety, loss of control, and fear for complications are often triggers of stress (17, 18). Unmanaged psychological distress and tension may lead to considerable complication during the cardiac catheterization, such as cardiac dysrhythmia, vessel spasm, and vessel laceration (19). Anxiety and uncertainty can also influence postoperative pain, pain medication and wellbeing (20). Therefore, it can be beneficial to reduce tension, anxiety and uncertainty with the aid of a psychoeducational intervention prior to the examination (21, 22). Studies have shown that stress-reducing interventions like music, therapeutic touch and massage have a desirable impact on physiological and psychological outcomes in patients undergoing cardiac examinations (23, 24). Preoperative cognitive and educative interventions were attested to positively influence the level of anxiety, wellbeing, treatment satisfaction, pain, and the amount of pain medication in the patient (25–30). It has been also shown that it is important to involve the patient into the perioperative pain management (21, 31). A sense of control and self-efficacy through psychoeducative interventions prior operations are associated with a faster reduction in post-operative pain and recovery (32, 33).

Although there is still only limited research on stress-reducing interventions in catheterization labs, a few studies on psychological preparation and video-based psycho-educative interventions in patients have shown beneficial results concerning pre- and perioperative distress, anxiety and coping as well as postoperative recovery and wellbeing (34–37). Less stressed and anxious patients may lead to less complications and reduced durations of cardiac catheterizations that could be beneficial for both patients and practitioners. A lower risk of complications and well-prepared patients may reduce the distress and pressure on the staff at the catheterization lab that in turn could be beneficial for patient safety and therapeutic outcome. To the best of our knowledge, there is no study protocol or study on stress-management in clinical settings that address both group—practitioners and patients—simultaneous. We expect a positive, bidirectional influence from both interventions to both intervention groups.

The objective of the study is to develop and implement an intervention for both practitioners and patients that aims to reduce the physical and psychological strain of a cardiac catheterization. This study tries to answer the following research questions:

Whether and to what extent are cardiac catheterization interventions physically and psychological stressful for both patients and practitioners?Whether and to what extent does a standardized video-based patient education lead to less stress, anxiety, surgical complications, postoperative hospitalization, as well as better recovery, compliance and well-being?Whether and to what extent can practitioners benefit from operational guidelines at the catheterization lab and a stress management intervention in terms of reduced stress during work at the catheterization lab and a faster recovery after a workday?

